## Methods

### Primary objectives

The primary objectives are to investigate the effect of BFRp and BFRpE on cardiovascular safety in comatose patients in the ICU and to investigate the applicability of such protocols as early motor intervention methods in intensive care.

### Secondary objective

The secondary objective is to investigate the effects of this intervention on neuromuscular adaptations, physical function, and quality of life of ICU coma-surviving patients.

### Study design

This study describes a protocol for a pilot study of a double-blind, randomized controlled clinical trial of applicability and intervention, with transverse temporality and a three-arm factorial intervention design in accordance with the Standard Protocol Items: Recommendations for Interventional Trials (SPIRIT) guidelines*.* The SPIRIT verification list can be found in the Additional File 1 and is represented in Fig. 1. The flowchart for the clinical trial is shown in Fig. 2.

**Fig. 1 Fig1:**
[figure not shown]
Schedule of enrollment, interventions, and assessments of a patient with 6 days of ICU permanence. ICU, intensive care unit; Hosp., hospital; T0, baseline time point—initial evaluation; T1, time point 1—evaluation during the first training session; S2, session 2—second training session; S3, session 3—third training session; S4, session 4—fourth training session; T2, time point 2—last training session; D1, day 1; D2, day 2; D3, day 3; D4, day 4; D5, day 5; D6, day 6; PM, passive mobilization; BFRp, blood flow restriction associated with passive mobilization; BRFpE, blood flow restriction associated with passive mobilization and combined with neuromuscular electrical stimulation

**Fig. 2 Fig2:**
[figure not shown]
Flowchart of the pilot clinical trial. ICU, intensive care unit; PM, passive mobilization; BFRp, passive mobilization associated with blood flow restriction; BFRpE, passive mobilization associated with blood flow restriction and combined to neuromuscular electrical stimulation

### Study setting

The clinical trial will be carried out in the teaching and research ICU at the *Irmandade da Santa Casa de Misericórdia de São Carlos*, located in the city of São Carlos, São Paulo, Brazil. This ICU consists of 10 beds, and there is an average of 40 patients admitted monthly. Adult clinical and surgical patients with all types of diseases are treated in the ICU, and the average length of stay is 8 days.

### Sample size rationale

A total of 30 participants were used for the sample size calculation of the clinical trial [43]. Therefore, a sample of 39 patients will enable 10% sample loss for each experimental group (PM/control, BFRp, and BFRpE). Based on a recruitment average of 24 patients per month, 20% of non-consent and 30% of non-previewed death or immediate discharge, we aimed to recruit 7.2 patients per month. The recruitment in a single ICU will allow the study to be completed in a minimal period of 6 months.

### Study population

The inclusion, non-inclusion, and exclusion criteria are shown in Table 1. All the criteria will be reevaluated before each training session, according to the clinical specificity of the criteria (Table 1). All non-included patients will be re-evaluated after 18 h of coma, except for patients whose hospitalization is longer than 18 h prior to ICU admission. In conclusion, all patients will be assisted by the ICU physiotherapy team. Additionally, the number of PM sessions or any type of physical therapy intervention in the peripheral muscle will be quantified to control the total volume of stimulus for each patient.

**Table 1 Tab1:** Inclusion, non-inclusion, and exclusion criteria of the study population

Inclusion criteria	Non-inclusion criteria	Exclusion criteria
1. Age of 25 to 55 years	1. Persistent arrhythmia with atrial fibrillation	1. Obese (BMI > 30 kg/m^2^)
2. Scores − 5 or − 4 according to the Richmond Agitation-Sedation Scale (RASS) or 3 to 5 in the Glasgow Comatose Scale	2. Pre-existing atrioventricular block or ventricular tachycardia	2. More than one thromboembolism risk factor
3. Maximal 18 h of coma in ICU admission or during critical care hospitalization	3. Recent acute myocardium infarction	3. Previous venous thrombosis and/or pulmonary embolism
4. Prediction of coma length between 2 and 6 days	4. Provisional or definitive pacemaker	4. Peripheral arterial vascular disease history or suspicion of lower limb arterial insufficiency
5. Prediction of 2 to 12 days of ICU permanence	5. Signals of intracranial hypertension	5. Severe cardiovascular instability and/or use of vasoactive drugs in infusion ≥ 0.5 mcg/kg/min
6. Daily protein consumption standardized for the ICU medical and nutrition teams	6. Neoplasia in chemotherapy treatment	6. Deep coagulopathy (prothrombin time (PT) > 2.5 times the normative values, activated partial thromboplastin time (APTT) > 2 times the normal or platelet count ≤ 50.000/μl)
	7. Non-consolidated fractures	7. Heparin intravenous infusion ≥ 2 UI/ml
		8. Fever or hypothermia
		9. Anemia
		10. Neurodegenerative disease
		11. Musculoskeletal disease

*ICU* intensive care unit

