### Study interventions

#### Peripheral muscle training

After T1, in view of the cardiovascular safety and applicability of PM, BFRp, and BFRpE, training sessions will be held twice a day, divided by 4 h [51]. The starting training leg will be randomly chosen at T1 and, from that, alternated in every training session. Patients will undergo the experimental protocol if they present controlled temperature (between 36.5 and 37.5 °C), stable blood pressure (> 100 and < 150 of SBP and > 60 and < 100 of DBP), SpO_2_ > 90%, respiratory rate (RR) < 25 rpm, and HR > 60 and < 140 bpm [55].

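### Changeable ICU states sit in Table 1's Exclusion column and are re-checked before every session, so a randomised patient who develops one is, by the label, removed; the article never says the session is merely held

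*Protocol article*

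**What the plan says.** Three parts of the protocol article bear on who stays in the study.

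- **Study population and Table 1.** "The inclusion, non-inclusion, and exclusion criteria are shown in Table 1", as three separate columns, and "All the criteria will be reevaluated before each training session, according to the clinical specificity of the criteria (Table 1"). The Exclusion column includes "Severe cardiovascular instability and/or use of vasoactive drugs in infusion" at or above 0.5 mcg/kg/min (item 5), deep coagulopathy (item 6), heparin infusion (item 7), "Fever or hypothermia" (item 8) and anemia (item 9). It also holds traits known at entry, such as obesity and neurodegenerative disease.
- **Peripheral muscle training.** "Patients will undergo the experimental protocol if they present controlled temperature", given as 36.5 to 37.5 °C, and "stable blood pressure", given as a systolic and a diastolic range. Oxygen saturation, respiratory rate and heart rate limits follow. This section does not mention exclusion.
- **Cardiovascular safety and applicability of peripheral muscle training.** After an interruption during training, other than for deep venous thrombosis, two further attempts are made before the patient is withdrawn. The article then calls that outcome exclusion and counts the protocol as unsafe for that patient.

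The Sample size rationale gives the planned allowance: "a sample of 39 patients will enable 10% sample loss for each experimental group".

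**The concern.** Fever, a rise in vasoactive dose or a fall in platelets is part of the course of an ICU stay. If such a state excludes a patient who has already been randomised, membership of the analysed groups depends on what happened after randomisation. The arms differ in cuff occlusion and electrical stimulation, and the Background names unknown cardiovascular repercussions as a reason for the study. Losses through instability could therefore be related to the assigned treatment, and the groups left for comparison would no longer be those that randomisation formed.

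The exposure is mainly on the secondary outcomes: muscle thickness and quality at T2, strength, physical function, and quality of life at 6 and 12 months. Daily scans made before an exclusion could still be used. The Discussion allows the last available assessment to stand in after unforeseen discharge or death, but does not mention patients excluded on a re-check.

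**Working it through.** **1. When the checks happen.** Sessions run twice a day, and the predicted coma length at entry is 2 to 6 days. That is about 2 × 2 = 4 to 2 × 6 = 12 pre-session checks per patient. Randomisation uses the baseline muscle thickness and so precedes training; the checks therefore fall almost entirely after it.

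**2. What a failed check leads to.** Setting the sections side by side:

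| State | Table 1 | Peripheral muscle training | Same state under both rules? |
|---|---|---|---|
| Abnormal temperature | Exclusion item 8, no threshold | Condition for undergoing the protocol (36.5 to 37.5 °C) | Yes |
| Haemodynamic instability | Exclusion item 5, severe, or vasoactive dose ≥ 0.5 mcg/kg/min | Condition for undergoing the protocol (SBP > 100 and < 150; DBP > 60 and < 100) | Unclear: item 5 may be a higher tier |
| Coagulopathy, heparin, anemia | Exclusion items 6, 7, 9 | Not mentioned | No |

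No sentence says that failing a Table 1 item only holds the session. The one place where the article uses *exclusion* for a patient already in training is the safety section, where it means withdrawal. Read that way, a patient whose saturation falls below 88% during training gets two further attempts, while a patient who is febrile before a session gets none.

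**3. The qualifier.** The words on clinical specificity can limit which items are re-checked. The 18 h entry limit and fixed traits need no repeat. They do not state the consequence of failing an item that can change.

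**4. Benchmark against the plan's own allowance.** Inputs: 39 patients planned, 30 in the calculation, 10% loss per group; equal arms are my assumption.

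- Planned arm size: 39/3 = 13. Stated allowance: 0.10 × 13 = 1.3 patients. One loss is 1/13 = 7.7%; two are 2/13 = 15.4%, above the allowance.
- Head-count margin: 30/3 = 10 and 13 − 10 = 3 patients, or 3/13 = 23.1%. Four losses are 4/13 = 30.8%, above the margin.

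The two margins differ because 39 is more than a 10% loss needs: 30/(1 − 0.10) = 33.3, rounded up to 34. Both are counted before any death or early discharge. They show how little room there is, not how many patients would go.

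**5. Illustration only.** The documents give no rate of failed checks. If each check failed independently with probability p, and one failure excluded, the share excluded over s checks would be 1 − (1 − p)^s:

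| Assumed p | s = 4 | s = 12 |
|---|---|---|
| 1% | 4% | 11% |
| 2% | 8% | 22% |
| 5% | 19% | 46% |
| 10% | 34% | 72% |

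Repeated checks in one patient are likely to be correlated, so this is not a forecast. If a failed check only holds the session, every cell is zero.

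**The case against.** The strongest reply is that removal is inferred from a column heading. The Study population section says the criteria are re-evaluated; it never says that a patient who fails is withdrawn, loses assessments or leaves the analysis. The heading is also a weak guide: the Exclusion column contains fixed entry traits, and the Non-inclusion column contains states that can arise later, such as intracranial hypertension. The sections can be read together so that a failed check means no session at that time. A design that gives two further attempts after instability during training is unlikely to intend permanent removal for one febrile morning. What is left would be operational detail that an article may leave to the full protocol.

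Much of this stands. Removal is not spelled out. The overlap is clear only for temperature; even there a two-tier reading is conceivable, though the article gives no fever threshold that would separate the tiers. No rate can be derived. This is a pilot whose primary objectives are safety and applicability, and the first-session cardiovascular measurements are largely untouched because that session immediately follows baseline.

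The reply does not dispose of the point. The article states a per-session re-check of items it labels Exclusion, uses that word for withdrawal elsewhere, and nowhere states a session hold for a Table 1 failure. Staff who follow the text as labelled would remove the patient.

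**Conclusion.** The point holds as a real ambiguity with a harmful reading, at medium confidence. By its label, Table 1 removes randomised patients who develop a changeable state, and the article offers no stated alternative for those items.

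A reader might infer three stronger things that the documents do not support:

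- **That the plan expressly drops these patients from follow-up and analysis.** It does not say so.
- **That it contradicts itself on blood pressure as well as temperature.** Severe instability may simply be a higher tier than an out-of-range reading.
- **That losses will exceed the allowance.** The number affected is unknown and may be zero.

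The size is therefore conditional. If the label is followed, and arms are equal at 13, the second exclusion in an arm passes the stated 10% and the fourth passes the head-count margin. The effect would fall on the secondary outcomes. It is worth correcting because the correction is cheap and closes a route to treatment-related loss after randomisation.

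**What to change.** Separate three things that the article now runs together.

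1. **Entry.** Use Table 1 to decide eligibility before randomisation only.
2. **Pre-session safety check.** Keep re-checking every criterion that can change, from both the Non-inclusion and the Exclusion columns, together with the limits in Peripheral muscle training. This covers new arrhythmia or conduction block, infarction, pacemaker, intracranial hypertension, chemotherapy, fracture, thromboembolic risk or event, limb arterial insufficiency, instability or vasoactive dose, coagulopathy, heparin, abnormal temperature and anemia. Coma depth stays a check, and waking ends training as already planned. A failed safety check postpones the session or stops training, and the reason is recorded.
3. **Follow-up and analysis.** State that neither a failed pre-session check nor a withdrawal from training under the safety section removes the patient from the planned assessments or from the analysis by assigned arm. The safety section's counting of unsafe protocols stays as it is.

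The cost is a short clarification. No safety check is dropped and no new assessment is added. The downside is that some analysed patients will have had fewer sessions, which may dilute the difference between arms.

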### Experimental design

#### Recruitment procedures

Initially, all hospitalized patients in the ICU will be assessed according to the inclusion criteria of the study. After screening, the legal representative will be interviewed and invited to be a participant in the study. Following consent, the legal representative will answer the functional performance of the basic activities of daily living through the Barthel Index [44] and the quality of life through the Medical Outcome Study 36 – Item Short Form Health Survey (SF-36) questionnaire [45, 46]. Following that, the patient will undergo other initial evaluations (T0) within a 23-h period after admission to the ICU or coma identification in the ICU hospitalization for the baseline demographic characterization, clinical, cardiovascular, and neuromuscular.

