##### Physical function adaptations

Physical function will be assessed 12 h after T2 and in the ICU and at hospital discharge through the Physical Function in Intensive Care Test Scored (PFIT). Lastly, during home follow-up, functional motor performance of basic activities of daily living will be evaluated using the Barthel Index, 6 and 12 months after hospital discharge, by telephone.

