##### Quality of life adaptations

Quality of life will be measured simultaneously with basic activities of daily living performance, using the SF-36 questionnaire, which is validated in Portuguese and Brazilian culture and is reliably applicable by telephone [53, 54].

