## Statistical analysis

After data collection, participants will be distributed into subgroups by periods in coma (2, 3–4, 5–6 days), in alertness (1–2, 3–4, 5–6 days), and in ICU permanence (3–4, 5–6, 7–8, 9–10, 11–12 days). The normality of data will be analyzed using the Shapiro-Wilk test. One-way analysis of variance (ANOVA) will be used for intra-group comparisons in T0. A mixed-model analysis will be used for each dependent variable, whereas group and time will be considered as fixed factors and subject as the random factor. In case of significant *F*, the Tukey adjustment will be applied for multiple comparisons. In the event of a non-normal data distribution, a Kruskal-Wallis test will be applied to test for the differences in baseline values and the Friedman test to analyze the repeated measures. The adjusted *p* values will be calculated using the Hommel procedure [48]. Effect sizes between and within groups will be calculated using Cohen’s *d* [89]. The minimal clinically important difference will be assessed with distribution-based methods [90]. The statistical significance will be assessed at *p* < 0.05. All analyses will be performed using R 3.6.2 (The R Project for Statistical Computing, 2019) in R-studio 1.3.443 (RStudio Inc., Boston, MA, USA).

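### If the T0 proxy scores enter the mixed model as repeated measures, Barthel and SF-36 change from T0 to 6 and 12 months mixes recovery with a probable change of respondent

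*Protocol article*

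**What the plan says.** In the Protocol article, Recruitment procedures, the representative is approached first: "After screening, the legal representative will be interviewed and invited to be a participant in the study". After consent, "the legal representative will answer the functional performance of the basic activities of daily living through the Barthel Index [44". The second instrument is given to the same person in the same sentence: "and the quality of life through the Medical Outcome Study 36 – Item Short Form Health Survey (SF-36) questionnaire". The T0 values of both instruments are therefore proxy answers.

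Under Physical function adaptations, functional performance during home follow-up is "evaluated using the Barthel Index, 6 and 12 months after hospital discharge, by telephone". Under Quality of life adaptations: "Quality of life will be measured simultaneously with basic activities of daily living performance, using the SF-36 questionnaire". Neither section says who answers the call. The abstract describes these follow-up contacts as a re-assessment, and the secondary objective concerns patients who survive the coma.

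Under Statistical analysis, each dependent variable gets a mixed model in which "group and time will be considered as fixed factors and subject as the random factor". In addition, "Effect sizes between and within groups will be calculated" as Cohen's d. If data are not normal, the repeated measures are analysed with the Friedman test. The section does not list the time points that enter the model for Barthel or SF-36, and it does not distinguish a proxy value from a patient's own answer.

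**The concern.** A change score means something only if the same thing is measured in the same way at both ends. Here the first value comes from a third party describing a comatose patient, and the later values probably come from the patient. The SF-36 covers bodily pain, vitality and mental health, which an outside observer has to infer. If representatives systematically rate higher or lower than patients rate themselves, that difference appears in every arm as decline or recovery.

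Two planned results are exposed: the part of the time effect that spans T0 to follow-up, and any within-group Cohen's d taken from T0. The article says the pilot will inform the design and sample size of a later trial, so a false effect size could be carried forward.

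**Working it through.** The plan states no figure on this point, so there is nothing to reproduce. The check compares the sections and then sizes the effect under stated assumptions.

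**1. What is fixed and what is inferred**

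| Item | T0 | 6 and 12 months |
|---|---|---|
| Respondent | Legal representative (stated) | Not stated; probably the patient |
| Mode | Not stated for the questionnaires; the representative is interviewed at recruitment | Telephone (stated) |
| Place in the model | Not stated | Not stated; a group-and-time model applies to each dependent variable |

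The patient is the likely follow-up respondent for two reasons. The proxy arrangement appears only in the recruitment text. The target is also the quality of life of coma survivors, with telephone use of the SF-36 justified by its properties in ICU patients.

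**2. Spurious within-group effect**

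Let b be the offset between proxy and patient answers, with no true change. Then d = b / SD, using the SD at a single visit. Neither b nor SD is in the documents. Assume SD = 20 on the 0-100 scale and b = 3 to 10 points:

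- 3 / 20 = 0.15
- 5 / 20 = 0.25
- 10 / 20 = 0.50

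**3. False-positive rate of a within-group test**

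Simulation of 20,000 runs with no true change, an assumed correlation of 0.5 between visits, and offset b added at 6 and 12 months equally in every arm. The test is a paired t test of T0 against 6 months, two-sided 0.05. Thirteen per arm is 39 / 3 and ten per arm is 30 / 3, from the sample size rationale.

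| Offset (SD) | 13 per arm | 10 per arm |
|---|---|---|
| 0 | 5% | 5% |
| 0.2 | 10% | 9% |
| 0.3 | 17% | 14% |
| 0.5 | 38% | 29% |
| 0.8 | 75% | 61% |

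Deaths would leave fewer patients at follow-up. That lowers these rates but leaves the expected mean shift in SD units unchanged.

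**4. What is not affected**

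In the same simulation, the mean difference between two arms in T0-to-6-month change stays at about 0, with rejection at about 5% for every offset. The 6-to-12-month within-group test also stays at about 5%. Algebraically, if a share p of each arm answers for itself, the arm mean shifts by b × p, and the between-arm difference is b × (p1 − p2). This is zero when p1 = p2.

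**The case against.** The strongest reply is that the text does not put T0, 6 and 12 months into one model. The Statistical analysis section names T0 only for the baseline comparison. Table 2 describes the Barthel variable as performance after hospital discharge, by telephone interview. A model of the 6- and 12-month values alone, with T0 used descriptively, fits the text as well. This stands, and it makes the point conditional. The condition is still plausible: the follow-up is called a re-assessment, Table 2 labels both outcomes as adaptations, and within-group effect sizes are announced without restriction.

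A second reply is that a proxy baseline cannot be avoided in comatose patients, and that the article addresses telephone use of both instruments. Both parts are right. The proxy is not the fault. The fault would lie in treating its answer as an earlier measurement of the same kind.

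A reader might infer three stronger things that the documents do not support:

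- **That mode and respondent certainly change.** The mode of the T0 questionnaires is not given, and the follow-up respondent is not named. If the same representative answered every call, the respondent part would disappear.
- **That the whole time effect is uninterpretable.** The 6-to-12-month contrast is by telephone at both ends and can be read if the respondent is constant.
- **That the arm comparison is biased.** The stated hypothesis on function and quality of life is between groups, where a common offset cancels. Bias needs a different respondent mix by arm. A gap of 20 to 40 percentage points with a 10-point offset would give 10 × 0.2 = 2 to 10 × 0.4 = 4 points; with a 3-point offset it would be 0.6 to 1.2. At 13 per arm such a gap is about 3 to 5 patients. Nothing in the article suggests it would occur.

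**Conclusion.** The point holds in a limited form. If T0 is analysed as a repeated measure, the T0-to-follow-up time effect and the within-group Cohen's d for Barthel and SF-36 confound recovery with a probable change of respondent and a possible change of mode. The plan as published does nothing to prevent that.

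The size depends on an offset that the documents do not give. Under the assumed 3 to 10 points and SD of 20, the spurious d is 0.15 to 0.50. The false-positive rates also rest on the assumed visit correlation of 0.5.

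The Friedman fallback makes the condition matter somewhat more. It tests time within subjects and contains no arm comparison, so with T0 included the affected effect would be the one tested.

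The randomised comparison is not undermined in expectation while the respondent mix is similar across arms. These are two secondary outcomes of a pilot whose primary objectives are cardiovascular safety and applicability. The point is worth correcting because the correction is nearly free.

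**What to change.** For Barthel and SF-36, state in the Statistical analysis section that:

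1. only the 6- and 12-month values are outcomes in the mixed model;
2. arms are compared at those two times, with the T0 proxy score as a baseline covariate;
3. T0 is not one of the repeated times in the Friedman fallback for these outcomes;
4. within-group effect sizes from T0 are not reported as recovery.

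Under Physical function adaptations and Quality of life adaptations, name the intended respondent for the calls, and record who actually answers each one. The respondent mix can then be shown by arm, which checks the condition on which the between-arm contrast rests.

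The cost is a few sentences and one extra field on the call form. The T0 proxy score is already collected, and no added proxy interviews at follow-up are needed; these would lengthen each call and yield two versions of each outcome. The small downside is that no within-group change from the state the proxy describes at T0, presumably before the illness, is reported for these two outcomes.
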